**Fig. 3 Fig3:**
[figure not shown]
Trial flow of the four study conditions. CR = cognitive reappraisal training; CR + AFE = cognitive reappraisal training enhanced by instructions to deliberately display anti-depressive facial expressions; AFE = facial muscle training focusing on anti-depressive facial expressions

*CR*. To work with the cognitions, participants are instructed to respond to each of them in three steps. First, the screen will display three statements expressing *rejection* of the depressogenic cognition or *approval* of the anti-depressive cognition. Second, three statements *affirming* the rejection/approval, and third, three *self-supporting* statements will be presented on the screen. In each step, participants will choose the subjectively most fitting statement by selecting it on the screen and reading it aloud. To conclude the trial, participants again read aloud the affirming and self-supporting statement (depressogenic cognition training) or all three positive statements (anti-depressive cognition training) they have selected in a combined fashion.

*CR + AFE.* In the CR + AFE condition, participants will follow the same three steps as in the CR condition, except that they are instructed to mirror them with congruent kinesthesia including mime, posture, and gesture. Step 1 will be accompanied by rejection/approval, Step 2 by approval/confidence, and Step 3 by joy (trials 1 to 10) or pride (trials 11 to 20).

*AFE*. In the AFE condition, participants are instructed to first experience the elicited emotion, and then counteract depressogenic cognitions/strengthen anti-depressive cognitions by tensing or relaxing relevant facial muscles, for example, the forehead (i.e., the area between the eyebrows). In total, four different facial muscles are targeted in this condition: (1) m. corrugator supercilii or the “frowning muscle,” (2) m. zygomaticus, the muscle relevant to lifting the corners of the mouth to smile, (3) m. orbicularis oculi, a circular muscle around the eye activated when smiling, and (4) m. masseter or the “chewing muscle,” used when clenching one’s teeth, as well as different combinations of all four facial muscles. The exact number of combinations and repetitions can be found in Supplementary Table 1. When participants perform the respective expression, the study therapist commands the app to zoom-out depressogenic and zoom-in anti-depressive statements on the smartphone screen according to the intensity of participant’s performance as trainer-operated biofeedback.

#### Training for the sham control condition

For the sham control condition, the training consists of allocating geometric forms to a target object based on either their color (Training Phase 1) or their shape (Training Phase 2) in order to control for effects of interacting with a study therapist and a smartphone, as well as activation related to study participation.

### Measures

#### Demographic and health-related information, screening, and diagnostics

Demographic and health-related variables assessed include age, date of birth, German language skills, nationality, gender, height, weight, academic degree, professional occupation, current academic field, relationship status, lifetime diagnosis of a psychiatric disorder, as well as history of and current psychotherapy and medication treatment.

The PHQ-8 will be used to screen for current depressive symptomatology during online screening (T0). The 8-item self-report measure assesses the frequency of eight of the nine criteria for depression according to the DSM-5 [1] during the previous two weeks on a four-point Likert-scale (0 = *not at all* to 3 = *nearly every day*). In contrast to the PHQ-9 [49], the PHQ-8 does not assess suicidality or self-injury. To ensure provision of adequate psychological support when necessary, we exclusively assessed suicidality/self-injury while face-to-face with participants. Previous studies showed comparable validity of the PHQ-8 and PHQ-9 in assessing depression [40, 50]. The items of the PHQ-8 can be summed up to a total score with a maximum of 24. A score ≥ 10 indicates clinically relevant depression [40].

To assess the presence of psychiatric disorders according to DSM-5, we will conduct the SCID-5-CV (German version) as part of the diagnostic session (T1). It has demonstrated acceptable to excellent reliability [39]. For a more in-depth overview of the *severity of depressive symptoms*, the German version of the GRID-HAMD [51] will be used. The GRID-HAMD represents a revised version of the HAMD [52] and integrates a guideline for the semi-structured interview. Moreover, the GRID-HAMD assesses the frequency (4-point scale from *absent* to *almost all of the time*) as well as the intensity of symptoms (5-point scale from *absent* to *very severe*) during the previous week, allowing a dimensional rating of the severity of depression. In the current study, we will use the 21-item version of the GRID-HAMD complemented with the items, *helplessness*, *hopelessness*, and *worthlessness* of the HAMD-24. The GRID-HAMD has shown both validity, and acceptable to excellent reliability (Cronbach’s alpha = 0.78, ICC = 0.95; [51]). During the diagnostic session, the first part of the SCID-5-CV assessing current depressiveness (SCID-5-CV chapter A) and the HAMD will be combined to maintain a more pleasant conversation flow during the interview. While this requires a change in the order of HAMD-items, no changes to content will be made. The new item order of the combined tool can be found in Supplementary Table 2.

#### Primary outcome

*Current depressed mood* will be assessed using an eleven-point Likert scale from 0 to 10, with 0 = *no depressed mood at all* and 10 = *very strong depressed mood*, respectively. Participants will submit twelve mood ratings via smartphone during the preparatory phase, with one rating after each emotion induction, and one rating immediately before the first training item, as well as twice during each trial (once after the initial statement has been read out aloud and once after the last step of the trial has been completed). Thus, a total of 96 mood ratings for depressed mood will be compiled for each participant.

#### Secondary outcomes

Similarly to current depressed mood, *current positive mood* will be assessed by means of an eleven-point Likert-scale from 0 to 10, with 0 = *no positive mood at all* and 10 = *very strong positive mood*, respectively. The number of mood ratings for positive mood is the same as for depressed mood, adding up to a total of 96 positive mood ratings over the course of the training.

Beyond clinical interviews and single-item mood ratings, questionnaires will be administered at several points during the training. The German version of the Centre for Epidemiological Studies Depression Scale (CES-D; [53]) will be administered to assess self-reported symptoms of depression during the previous week. The 20 items are rated on a four-point Likert scale from 0 (*some of the time*) to 3 (*most of the time*). A total score can be obtained by summing up the items, with a score greater than 22 considered to be clinically relevant [53]. The CES-D has demonstrated good reliability and validity in several studies [54, 55].

*Current suicidality* will be assessed with a single, self-developed item on a six-point Likert scale from 1 (*no suicidality*) to 6 (*suicide attempt*).

*Emotional state* will be assessed with Part A of the Self-Report Instrument for the Assessment of Emotion-Specific Regulation Skills (ERSQ-ES; [56]). This scale measures feelings and mood during the previous week with 50 items on a 5-point Likert scale from 0 (*never*) to 4 (*all the time*). *Dysfunctional attitudes* will be assessed with the German short version of the Dysfunctional Attitude Scale version A (DAS-18-A; [57]). The short version consists of 18 items assessing respondents’ agreement with dysfunctional attitudes that are typically found among individuals with depression (e.g., “My value as a person depends on what others think of me”) during the last week on a 7-point Likert scale from 1 (*fully disagree*) to 7 (*fully agree*). The DAS-18-A has shown good validity and reliability in patients with depressive symptoms and in healthy individuals [57].

In addition, the 21-item German version of the Automatic Thoughts Questionnaire-Revised (ATQ-R; [47]) will be administered. The ATQ assesses the frequency of positive and negative automatic thoughts (e.g., “My life is a mess”) during the previous week on a five-point Likert scale from 1 (*not at all*) to 5 (*all the time*). It has shown acceptable to good reliability in the general population (Cronbach’s alpha = 0.67-0.86) and good reliability in a patient sample (Cronbach’s alpha = 0.84-0.94; [47]).

#### Feasibility measures

We will assess treatment integrity, compliance, usability, and acceptability to determine the feasibility of our intervention.

*Treatment integrity* is defined as study therapists’ adherence and competence (in accordance with [58]. A subsample (10%) of video-recorded training sessions will be used to rate treatment integrity. Adherence with the manual and therapist competence will be rated on a five-point Likert scale from 1 (*not at all*) to 5 (*very much*).

*Compliance* of participants in terms of commitment to the training will be rated by study therapists on a five-point Likert scale from 1 (*not at all*) to 5 (*very much*).

The *usability* of the intervention smartphone app will be operationalized with the short form of the User Experience Questionnaire (UEQ-S; [59]) and one self-generated item asking participants about the comprehensibility of the instructions in the app on a four-point Likert scale from 1 (*not at all*) to 4 (*very*). The UEQ-S consists of eight pairs of terms related to user experience with opposite meanings (e.g., complicated – easy) that are rated on a seven-point Likert scale from − 3 (*fully agree with negative term*) to + 3 (*fully agree with positive term*). The UEQ-S has two subscales (pragmatic quality and hedonic quality), and an overall indicator of user experience can be computed.

*Acceptability* of the training is operationalized with the ‘hedonic quality’ scale of the UEQ-S and 12 additional self-generated items, all rated on a four-point Likert scale from 1 (*not at all*) to 4 (*very*), and four open questions will be directed toward participants to gain feedback and suggestions for app improvement (see Supplementary Table 3 for the whole measure). Additionally, eight open-ended questions will be asked by the study therapist after the first and after the second training phases.

#### Kinesthesia measures

For the analysis of (affective) facial expression, videos will be recorded using the built-in smartphone camera, which will be positioned in front of the participant at a distance of approximately 40 cm. A video for each emotion induction and training trial will be recorded, adding up to a total of 44 videos. In addition to these smartphone videos, two high-resolution RGB cameras (Sony SRG-300 H) will be used, one of them positioned directly in front of and the other to one side of the participant, both approximately 1.2 m away. Together, the cameras will record the participant’s face and upper body. We will extract information on facial expression (i.e., facial action units, eye gaze, head position, and facial emotions) from recordings of the front camera and information on body posture from the side camera. A third RGB camera will focus on the study therapist during the diagnostic session and training for adherence checks. Additionally, we will use an Azure Kinect depth camera (Microsoft, Redmond, WA, USA) to estimate participants’ body posture using the Azure Body Tracking SDK.

#### Further psychophysiological measures

EMG (bipolar) of the M. corrugator supercilii, M. zygomaticus major, M. orbicularis oculi, and M. masseter (the latter only in the AFE condition) will be assessed with the Biopac MP160 (Biopac Inc. Goleta, CA, USA) system. EMG measures will be assessed in a subsample (100% of the participants in the AFE condition and randomly chosen 50% of the participants in the other three conditions) to reduce participant burden. To assess kinesthesia markers potentially relevant to depression, also sensor-based physiological data will be recorded. We will use the Biopac MP160 system to record electrocardiogram (ECG) and respiration signals, from which we will extract heart rate (variability) (bipolar) and respiration rate (variability). In addition, we will use a novel, non-invasive radar-based technology positioned approximately 0.5 m behind participants to assess respiration and heart rate (variability). Here, for cross-validation purposes, we will employ two radar systems, a 24 GHz and a 61 GHz system. The radar-based technology has been shown to be a valid contactless measure of respiration and heart rate [60].

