#### Efficacy of the reappraisal training augmented with facial expressions

In order to study the effectiveness of the EmpkinS-EKSpression app-based interventions, generalized linear models (GLMs) of the between-subject factors “diagnostic group” (with depression vs. without depression) and “intervention condition” (CR vs. CR + AFE vs. AFE vs. sham control), as well as the within-subject factor “time of assessment” will be applied in a stepwise fashion.

Regarding the primary outcome of depressed mood, we will first examine whether the mood induction phase *induces* depressed mood using a paired *t*-test with the pre- and post-mood-ratings as dependent variable (manipulation check). Further, hierarchical linear models (HLMs) will be implemented to assess whether the EmpkinS-EKSpression app-based interventions are effective in *reducing* depressed mood. As a first step, we will compare the CR condition with the sham control condition and the CR + AFE with the CR condition to study whether cognitive reappraisal training can be augmented with anti-depressive kinesthesia. As a second step, we will compare the AFE condition with the sham control condition. For continuously assessed secondary outcomes (i.e., positive mood, app data), corresponding analyses will be conducted.

With regard to secondary outcomes (i.e., GRID-HAMD, CES-D, current suicidality, ERSQ-ES, DAS-A, ATQ-R) assessed at pre-treatment, post-treatment, and/or follow-up, as well as pre/post mood-ratings, we will implement mixed analyses of variance (ANOVAs), again with the between-subject-factor, “study condition” (CR, CR + AFE, AFE, sham control) and the within-subject factor, “time.” Feasibility measures (treatment integrity, compliance, usability, acceptability) will be descriptively analyzed and contrasted between study conditions utilizing one-way ANOVAs. Finally, changes in kinesthesia and other psychophysiological measures over the course of the intervention, as well as differences between diagnostic groups and intervention conditions will be examined using, again, HLMs. All analyses will be conducted using the whole sample, as well as with the added between-subject-factor, “diagnostic group” (with vs. without depression). All analyses will be conducted with a significance level of α = 0.05. One-tailed tests will be used when the algebraic sign of the test statistic is specified; otherwise, two-tailed tests will be used.

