Major limitations of the study include the short intervention period. It is unlikely that we will achieve long-term effects on depressed mood or effects on overall depressive symptom severity with a single intervention. Instead, the current study can serve as a proof of principle. If beneficial effects on depressed mood are found, future research should further develop the intervention (e.g., by introducing extended intervention periods) to achieve more sustained effects on depressive symptoms. Second, the planned time-consuming setup and ongoing collection of physiological data proposed here might distract participants from the intervention itself. Third, because the training is carried out in a highly standardized laboratory setting, this will limit the ecological validity of our results. Future studies should use an automated version of the training to investigate its efficacy in ambulatory settings. Fourth, we currently use standardized sets of stimulus statements, unlikely to be equally relevant for all participants. Fifth, facial EMG sensors and their cables might disturb the encoding of visual features in facial expression video data. Therefore, we are currently exploring ways of assessing EMG with wireless sensors and innovative, laser-based methods.

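### Facial EMG is worn by all of the AFE arm but by half of the other arms, so unadjusted facial-expression video contrasts with AFE carry half of any EMG effect, and AFE versus sham on mood is exposed only under stated conditions

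*Protocol article*

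**What the plan says.** - **Who wears EMG.** Under Further psychophysiological measures, facial EMG is recorded in "100% of the participants in the AFE condition and randomly chosen 50% of the participants in the other three conditions". The reason given for subsampling is "to reduce participant burden". The masseter site is used in the AFE arm only, which the footnote to Table 1 repeats. ECG and respiration are not described as limited to a subsample.
- **What the sensors may do.** The limitations in the Discussion state that "facial EMG sensors and their cables might disturb the encoding of visual features in facial expression video data". They also state that the "planned time-consuming setup and ongoing collection of physiological data proposed here might distract participants from the intervention itself".
- **Which contrasts involve AFE.** Under Efficacy of the reappraisal training augmented with facial expressions, the depressed-mood analysis continues: "As a second step, we will compare the AFE condition with the sham control condition". The same section examines kinesthesia with hierarchical linear models, both for change over the intervention and for differences between conditions. The factors it names are diagnostic group, condition and time.
- **When the sensors go on.** Under Procedure, the recording equipment is set up before the intervention starts. Under Smartphone-based intervention and Primary outcome, the first phase of the intervention is a preparatory phase with twelve mood ratings, ahead of mood induction and training.

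**The concern.** The EMG share is set by the design and tied to the arm, so randomising participants to conditions does not balance it. The article treats sensor interference as a general limitation and does not mention that exposure differs between arms. That difference turns a nuisance common to everyone into something a contrast with AFE can pick up.

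The clearest exposure is in facial-expression video. If electrodes and cables alter the extracted facial features, a difference between AFE and another arm is partly a difference in how many faces carry electrodes. The AFE electrodes also lie over muscles that this arm trains, so an artefact there is hard to tell from a training effect. For mood, the question is whether the additional burden of facial EMG could pass into AFE versus sham.

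**Working it through.** **Inputs.** 32 participants per condition and diagnostic group, hence 32 × 2 = 64 per condition; d = 0.5, two-sided alpha 0.05, power 0.80 (Participants). EMG shares are 1.00 in AFE and 0.50 in each other arm. The effect of wearing EMG, e (in SD units), is not given and is assumed over a range.

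**Step 1: the plan's own figure.** A two-sample t-test with 64 per condition and d = 0.5 has power 0.801, so the stated sample size reproduces with both diagnostic groups pooled. (With 32 per arm inside one diagnostic group, power is 0.504. That is not the issue here.)

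**Step 2: EMG wearers.** AFE: 64 × 1.00 = 64. Each other arm: 64 × 0.50 = 32, giving 96 wearers and 96 non-wearers over CR, CR + AFE and sham.

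**Step 3: bias in an unadjusted comparison of levels.** Under an additive effect, the arm means contain 1.00e and 0.50e:

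- AFE minus any other arm: (1.00 − 0.50)e = 0.5e.
- CR minus sham, and CR + AFE minus CR: (0.50 − 0.50)e = 0 in expectation.

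For one value per participant, 64 per arm, normal approximation:

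| Assumed e (SD) | Bias 0.5e (SD) | Share of d = 0.5 | Rejection rate, no true effect | Power at d = 0.5, bias toward null | Power, bias away from null |
|---|---|---|---|---|---|
| 0.1 | 0.05 | 10% | 0.059 | 0.72 | 0.88 |
| 0.2 | 0.10 | 20% | 0.087 | 0.62 | 0.92 |
| 0.3 | 0.15 | 30% | 0.136 | 0.51 | 0.96 |
| 0.5 | 0.25 | 50% | 0.293 | 0.29 | 0.99 |

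Without bias, the same approximation gives power 0.807.

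**Step 4: mood as change within person.** Suppose EMG shifts mood by s in the preparatory ratings and by s + g during training. An arm with EMG share p then has its mean change shifted by p(s + g) − ps = pg. The bias in AFE versus sham is 0.5g. If the shift is constant, g = 0 and it cancels. Bias of 0.5s remains only if raw levels are compared, or if the baseline is a rating made before the electrodes were fitted (Table 1 also marks depressed mood at T1).

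**Step 5: cost of removing the EMG effect, at d = 0.5.**

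- *Wearers only, 64 versus 32:* t-test power 0.63.
- *EMG status as an additive covariate, with e estimated from the 96 versus 96 split:* variance 1/64 + 1/64 + 0.25 × (1/96 + 1/96) = 0.0365, against 0.03125 unadjusted. Standard errors are 0.1909 and 0.1768, ratio 1.08. Power is Φ(0.5/0.1909 − 1.96) ≈ 0.745, against 0.807.

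**The case against.** The strongest reply concerns mood. Electrodes are already in place for the preparatory ratings, and time is a within-subject factor, so a constant EMG shift cancels in condition-by-time effects. This stands, and it limits the mood point to the two conditions in step 4.

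Two further points also stand. The distraction sentence in the Discussion covers the whole physiological setup, whereas only the facial EMG increment differs between arms; no text says that this increment affects mood. And the video sentence concerns facial expression, so body posture from the side camera or depth camera is not covered.

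A reader might therefore be tempted to conclude that the AFE versus sham mood result and every video comparison with AFE are biased by 0.5e, or that EMG would flatter AFE. The documents support neither. They give no size or direction for e, and distraction from the intervention could as well weaken AFE.

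It can also be said that covariates are commonly left to a fuller analysis plan. The absence of an EMG term alone would be no finding. What remains is a design feature the article itself fixes, an interference it itself concedes, and no acknowledgement that the two combine unequally across arms.

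A constant video artefact would likewise cancel in change from a recording made with sensors on. But the plan lists differences between conditions alongside change, and those differences are exposed.

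**Conclusion.** The point holds in limited form. Facial-expression video levels compared between AFE and any other arm carry 0.5e unless EMG is accounted for: 0.05 to 0.25 SD for assumed e of 0.1 to 0.5 SD. This is a structural risk, not a demonstrated bias.

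For AFE versus sham on depressed mood, the risk is conditional: it requires that EMG changes the response over the training, or that raw levels are analysed. CR versus sham and CR + AFE versus CR, which address whether reappraisal can be augmented, are balanced on EMG.

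The calculations assume additivity, full recruitment, pooled diagnostic groups and one value per participant; the repeated-measures models will have different absolute power.

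**What to change.** - **Facial-expression video.** Compare AFE with the other arms among EMG wearers (about 64 versus 32 per arm), or add EMG status to the hierarchical model. Wearers in the other arms are a random half, so the restriction introduces no selection by design.
- **AFE versus sham on mood.** Keep the main analysis and report a wearers-only sensitivity analysis beside it. If a model term is used instead, include EMG status and EMG-by-time, since a main effect alone does not remove an effect on change. State the assumption that EMG acts equally in all arms; it cannot be tested in AFE, where nobody goes without EMG.
- **Limitations.** State that EMG exposure differs by arm and that the AFE-only masseter electrode cannot be separated from the AFE effect by either method.

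The cost is precision: power of about 0.63 at d = 0.5 for wearers only, or a standard error about 8% larger with the additive covariate (power about 0.745). Recruitment and procedures stay as they are.
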